# Daily socket comfort in transtibial amputee with a vacuum-assisted suspension system: study protocol of a randomized, multicenter, double-blind multiple N-of-1 trial

**DOI:** 10.1186/s13102-023-00694-4

**Published:** 2023-07-14

**Keywords:** Amputation, Elevated vacuum, Vacuum-assisted suspension, Active vacuum, Prosthetic suspension system, N-of-1 Trial

## Abstract

**Background:**

The main aim of this paper is to present the feasibility of rigorously designed multiple N-of-1 design in prosthetics research. While research of adequate power and high quality is often lacking in rehabilitation, N-of-1 trials can offer a feasible alternative to randomized controlled group trials, both increasing design power at group level and allowing a rigorous, statistically confirmed evaluation of effectiveness at a single patient level. The paper presents a multiple N-of-1 trial protocol, which aim is to evaluate the effectiveness of Unity, a prosthetic add-on suspension system for amputees, on patient-reported comfort during daily activities (main outcome measure), prosthesis wearing time, perception of limb-prosthesis fitting and stump volume and functional walking parameters.

**Methods:**

Multicenter, randomized, prospective, double-blind multiple N-of-1 trial using an introduction/withdrawal design alternating Unity connected/disconnected phases of randomized length on twenty patients with unilateral transtibial amputation. The primary outcome measure is the Prosthetic Socket Comfort Score (SCS), a validated measure of comfort, administered daily by an phone app designed for the study. Secondary outcomes measures will be collected during the 50 days period of the N-of-1 trial: (1) by the same app, daily for patient-reported limb-prosthesis fitting, stump volume variation, and daily wearing time of the prosthesis; (2) by a pedometer for the number of steps per day; (3) by blind assessors in the rehabilitation center during adjustment visits for functional walking parameter (L-Test, 6-minute walk test), and by the patient for the QUEST, and ABC-S. Effectiveness of the Unity system regarding SCS and daily secondary outcome measures will be tested by randomization test. The secondary outcome measures assessed during visits in the rehabilitation center will be analyzed by Non Overlap of All pairs. An estimate of the effect on the amputee population will be generated by aggregating each individual clinical trial (N-of-1 trial) by Hierarchical Bayesian methods.

**Discussion:**

This study protocol was designed to answer the question “which device is best for THIS patient" and to conclude at a group level on the effectiveness of a new devic, using a Multiple N-of-1 trial, which is promising but underused in prosthetics research so far.

**Trial registration:**

N° ID-RCB 2020-A01309-30 Clintrial.gov : NCT04804150 - Retrospectively registered March 20th 2021.

## Background

Lower limb amputation has a major functional impact and significantly reduces independence in daily life [1]. An adequate socket fit on the residual limb is essential to ensure the patient's comfort but may be impeded by stump volume variations. Movements of the residual limb in the socket may lead to pain, sores, poor prosthesis control, or simply lack of comfort resulting in a limitation of prosthesis use and a loss of mobility [2]. Fifty-seven percent of the amputee population are dissatisfied with the comfort of their prostheses [3, 4] this lack of comfort represents the main complaints in amputees [5].

Vacuum-assisted suspension systems (VASS) (or elevated vacuum systems or active vacuum systems) draw out air and create a negative pressure at the residual limb liner and socket interface. They were originally evaluated by Caspers in 1995 [6] to reduce residual limb volume loss. Benefits of the system found in the literature are many: (1) it increases negative pressure during swing phase for better fitting [7] ; (2) it reduces residual limb volume fluctuations which better protects from skin lesions [8]; (3) it enhances fitting and security during walking [9] ; (4) it optimizes balance (BERG scale) and functional walking parameters (Timed Up and Go Test, 6-minute walk test) [10]; and (5) a recent metanalysis suggests that it improves comfort and quality of life [5].

Although VASS require more maintenance, attention and skills for donning and doffing and may be difficult for older patients with amputation [11].

Prescribers have the choice between different VASS: for the WillowWood LimbLogic system^TM^ and the OttoBock Harmony system^TM^, the vacuum is created using a pump and exhaust valve between a knee sealing sleeve and the liner. The disadvantage is that the sealing sleeve must be worn up to the top of the thigh and therefore limits the knee's range of motion [5], keeps warm and creates hyperpressure on the patella.

On the other hand, Össur Unity^TM^ VASS system relies on a mechanical pump which draws air out from the socket at each step without a sealing sleeve. It uses a Seal-in liner with integrated seals on the middle part of the liner. The vacuum is created between the integrated seals and the distal part of the liner. Gholizadeh et al. evaluated the Unity system and found improved proprioception and comfort [12], but the study relied only subjective feedbacks and did not use a control condition. Other VASS have been assessed only in unecological environment (i.e. not within the natural environment of patient’s daily life), giving little insight into the effectiveness of the system regarding comfort and ecological daily use of the system. Therefore, studies using ecological outcome measures and targeting comfort rather than complications of wearing the prosthesis are needed. Ecological measures target patient’s daily life functioning and preoccupations, in his/her natural context and usual activities.

Trials on prosthetics face a number of challenges: (1) the heterogeneity of the amputee population makes it difficult to obtain comparable groups of sufficient size to detect a statistically significant effect (e.g.: in the 2016 VASS meta-analysis [13] the greatest sample was 18); (2) intra-patient variability due to pain, fatigue or due to artificial (in rehab center) versus ecological activities makes single assessment on a given day or in the rehab center not always representative of the patients’ true functioning; (3) differential response to the prosthetic (i.e. some patients presenting with a great benefit, while others showing no benefit or getting worse), is masked by relying on group means.

Multiple N-of-1 trials are increasingly used in drug trials [14] and may represent a turning point for prosthetic trials as well. Multiple N-of-1 trials are multi-cycle within-patient, randomized, double-blind, cross-over comparisons of an intervention (e.g.: a novel prosthesis) and placebo (or a usual prosthesis) measuring immediate treatment effects and using standardized measures of effect [14]. They provide evidence-based information on individual response to treatment and could be used to optimize the management of each individual patient, or to decide the funding of an additional prosthetic such as VAAS. N-of-1 trials can identify those patients who respond (i.e. show gains) - and those who don’t - to an intervention, for chronic, stable conditions, and are therefore well suited for studying prosthetics in the amputee population. In addition, multiple N-of-1 can be aggregated with high level of power to provide a population estimate of effect, but requiring a fraction of the sample size of the equivalent parallel arm in Randomized Controlled Trials (RCT). This particularity is a chance for research on prosthetics where most studies lack power due to small sample sizes. N-of-1 trials are now recognized as Level 1 Evidence by the Oxford Centre for Evidence-Based Medicine [15]. Table 1 adapted from Nikles et al [14], presents the advantages and necessary conditions for multiple N-of-1 trials.

**Table 1 Tab1:** Rationale for the methodology

**Conditions to use a multiple N-of-1 trial (adapted from Nikles and Mitchell** [16]**)**
• The patient's condition is stable during the phases with minimal fluctuations over time • The treatment does not change the condition but only treats the symptoms • The intervention has a short wash-out, i.e. its effect disappears when it is removed • The therapeutic effect is quick when the treatment is applied and quickly stops when it is removed, i.e. on/off effect • There is no cumulative effect of the treatment
**Advantages to use a multiple N-of-1 trial methodology**
• Patients lost to follow-up or out of the study can still be analyzed on the phases already completed • Possibility to work with heterogeneous samples for individual interpretation • The 2 arms of the treatments are perfectly matched • All patients test both treatments (no ethical problem) • At group level: statistical significance with smaller sample size • Patient-by-patient analysis takes into account inter-individual variability by analyzing each N-of-1 trial to determine is a patient is a responder, non-responder, or is aggravated • Highlights possible inter-individual variability in the global results • Allows to extract an effect even in presence of large intra-individual variability (e.g.: patient performing variably because of pain, fatigue, unusual activity…) by measuring repeatedly the patient over time.
**Disadvantages to use a multiple N-of-1 trial methodology**
• Only treatments with true on/off effects can be explored and the condition must be stable. Therefore, any prosthetic/orthotic inducing cerebral plasticity (e.g.: thumb opponent splints in children) or requiring a long time for the patient to adapt/learn cannot be explored. This limits the range of prosthetic interventions that can be explored by multiple N-of-1 trials. • The population is smaller and may not be representative of the general population^a^. • Inability to explore statistically predictive factors^b^. • Inability to detect low-prevalence side effects.

^a^However, this problem is not specific to N-of-1 trials. Randomized controlled trials (RCT) claim in theory to provide a generalizable population outcome but they mask variability in response to treatment. Even in the most successful RCT study there are individuals whose behavior is not affected or is worsened by treatment, but these results are drowned out by a group mean.

^b^This is also true for randomized controlled trials (RCT). Power is calculated to demonstrate the effect of a treatment and not to determine predictive factors and responder characteristics.

The aim of the study is to evaluate the effectiveness of the Unity VASS on patient-reported comfort (using the Socket Comfort Score) during daily activities, in ecological environment, in patients with unilateral transtibial amputation blinded to the connection or disconnection of the Unity system, using a randomized, double-blind, multicenter prospective multiple N-of-1 trial. The secondary objectives are to evaluate whether Unity system leads to: (1) increased wearing time with the prosthesis, (2) increased number of steps per day, (3) decreased feeling of stump volume variation; (4) improved perception of limb-prosthesis fitting; (5) increased functional walking parameters.

## Methods & design

This multicentric prospective, randomized, double-blind, multiple N-of-1 trial, will include 20 patients recruited non-concurrently in 4 rehabilitation centers in France, in an 18-months period, representative of the overall French amputee population, in terms of patient’s characteristics and type of amputation performed by the local surgery teams. Because these centers have a large geographical recruitment, patient of all demographic and socioeconomic status will be represented Each patient will be referred by his/her private prosthetist to the inclusion center, which will allow to include patients, who do not have any medical or rehabilitation follow up anymore. Inclusion criteria are presented in Table 2. All concomitant care is allowed, apart from testing another new prosthetic device. Each patient will sign an informed consent, the consent will be collected by each main investigator of the center.

**Table 2 Tab2:** Inclusion and exclusion criteria

**Inclusion criteria**	**Exclusion criteria**
- Male or female aged >18 years old - Unilateral transtibial amputation > 6 months - Equipped with a Seal-in liner^a^ without VASS since at least 3 months - Equipped with a class II or III prosthetic foot^b^ compatible with the Unity system - ICF classification d4602 and/or d4608^c^ [17] - Presenting some discomfort in the socket evaluated by a SCS ≤ 7/10 - Availability of daily smartphone use and functional 4G connection	- Cognitive impairment impeding comprehension of the trial instructions - Patients who have already been equipped with the Unity VASS system in the past - Pregnancy - Adult under curatorship or guardianship - Patient with no health insurance - Severe comorbidities

*VASS* Vacuum-Assisted Suspension System, *ICF* International Classification Of Functioning, Disability and Health, *SCS* Socket Comfort Score

^a^Seal-in is an Össur liner, compatible with the Unity system

^b^Class II or III stand for ICF d4602 and d4608, respectively, in the French National Health system

^c^d4602 = moving outside the house and other building; d4608 = other specified activities related to moving in and out of other locations (i.e. physical activities, professional activities, etc..)

### Design

After the inclusion visit, a prosthesis (with an Iceross Seal-In™ liner) equipped with an Össur-compatible foot and a Unity system will be manufactured for each included patient. Each center will have one single prosthetist, trained and qualified for the Unity system by the Össur company, who will manufacture all the prosthesis of the trial but will be independent of the team performing the study. Each patient will wear the new prosthesis with the Unity system connected for 28 days, before beginning the N-of-1 trial. This acclimation period is necessary to adjust the prosthesis and obtain a stability in patient’s daily activities.

The N-of-1 trial will then last 50 days for each patient, following a design with random alternation of Unity connection and disconnection of minimum 7 days periods. This minimum period has been decided in order to include a weekend in each period, as patient’s activity level is expected to be variable between weekdays and weekends. Randomization will be performed on R, SCDA (Single Case Data Analysis) plug-in package, by an off-center independent operator. The randomization will use a phase length ABAB randomization (i.e. allowing periods of unequal duration, which allows to interpret results with individual statistical significance) rather than block randomization commonly used in drug trials. “A” is for Unity system disconnected, and “B” for Unity system connected (see Fig. 1). However, because the patient has to come to the rehabilitation center at each phase change which would not allow the patient and the assessors to be blind to the next phase content, phases of a duration >14 days will be further randomized into two half-phases (of 7 days minimum), of the same content i.e. either connected or disconnected. A placebo visit between the two half-phases will allow to keep the blinding. The maximum phase duration obtained by ABAB randomization is 29 days, which will be further randomized to half-phases of minimum 7 days, meaning that the maximum duration of a half-phase is 22 days.

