### Sample size calculation

#### Power calculation for each N-of-1 trial (i.e. each patient)

One method for calculating power in a single N-of-1 trial (i.e. for a single patient) is calculating the number of possible randomization assignments [25, 26] which depends on the type of randomization, the number of phases and the number of measurements per phase. The greater the number of possible assignments, the greater the possibility of detecting a treatment effect that exceeds the threshold of significance of 0.05 if an effect exists. With 4 true phase transitions, with a minimum duration phase of 7 days, a maximum study duration of 50 days, and 1 measurement per day, the number of assignments generated by this design is therefore 2300, allowing a significance of up to *p =* 0.0004 for each patient, as calculated on R package for single-cases [17].

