### Statistical analysis

#### Statistical analysis of each patient’s N-of-1 trial

Effectiveness of the Unity system regarding SCS and daily secondary outcome measures will be tested by randomization test [20, 28], using the mean of each phase. Randomization allows reliable statistical analysis of auto correlated data (such as data from N-of-1 trials) and allows to extract a statistical effect for each participant separately. Missing data points will be managed by multiple imputation method. In case of a rescheduled transition visit, the real transition date and not the initially scheduled one will be used.

The secondary outcome measures assessed during visits in the rehabilitation center will be analyzed by NAP (Non Overlap of All pairs) [21, 22]. NAP is an estimate of the probability that a randomly selected point in Phase B shows an improvement over a randomly selected point in Phase A with θ=Pr(YB>YA)+0.5×Pr(YB=YA). Since NAP's interpretation of effect size according to Cohen's rules (d=3.464⁎(1√(1-NAP)/.5) has been shown to be inadequate, Parker's criteria will be used [21] (effect present but small if NA*P =* 0.5-.65; moderate effect: .66-.92; large effect: .93-1.0.). NAP [21] will also be applied to daily outcome measures, in addition to randomization tests, to obtain an effect sizes.

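### The 7-day minimum guarantees a weekend in every phase but not an equal weekend share, and the phase-mean test does not correct for it: a minor, cheaply removable loss of per-patient precision

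*Protocol article*

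**What the plan says.** The Design section gives the reason for the 7-day minimum: "This minimum period has been decided in order to include a weekend in each period", because "activity level is expected to be variable between weekdays and weekends". The same section makes phase lengths random, "allowing periods of unequal duration, which allows to interpret results with individual statistical significance", and adds: "The maximum phase duration obtained by ABAB randomization is 29 days".

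The per-patient power section counts the schedules "with a minimum duration phase of 7 days, a maximum study duration of 50 days, and 1 measurement per day" and concludes that "the number of assignments generated by this design is therefore 2300". The significance level given there is a "threshold of significance of 0.05".

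The section on the statistical analysis of each patient's trial tests SCS and the daily secondary outcomes by a randomization test "using the mean of each phase". Neither that section nor the one on aggregation mentions a weekday/weekend term, weighting or stratification.

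**The concern.** The plan names a nuisance and offers one safeguard against it. Having a weekend in a phase is not the same as having the usual two weekend days in seven. When phase lengths are not whole weeks, connected and disconnected phases can hold different proportions of weekend days, and a comparison of phase means then carries part of the weekday/weekend difference.

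The individual result is a purpose of this trial. Each participant receives a personal statistical report, responders are compared with non-responders, and the Discussion suggests funding costly devices on individual significance. Extra noise in one patient's contrast cannot be averaged away within that patient. The calendar date of each daily entry identifies its day type, so this noise can be removed.

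**Working it through.** **Inputs.** From the article: 50 days, one measurement per day, four phases (ABAB) of at least 7 days, alpha 0.05, SCS target difference 2, intra-patient variance 2, inter-patient variance 5.3, 20 patients. Assumed, because the article does not give them: the weekend effect g, the day-to-day autocorrelation rho (0 or 0.3), a two-sided test, and the intra-patient variance of 2 read as the variance of daily scores (daily SD √2 = 1.41 points).

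**1. The plan's own figures.** Four lengths of at least 7 summing to 50 give C(25,3) = 2300 schedules. The smallest p is 1/2300 = 0.0004. The longest phase is 50 − 3×7 = 29 days. All three agree with the article.

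**2. Weekend share.** I enumerated 2300 schedules × 7 start weekdays. The contrast is the mean of the two B phase means minus the mean of the two A phase means.
- Every phase holds at least 2 weekend days, so the Design section's statement is true.
- The share per phase runs from 2/12 = 16.7% to 4/9 = 44.4%; a full week has 2/7 = 28.6%.
- The B-minus-A difference in share has mean 0 over start weekdays and SD 6.7 percentage points. It exceeds 10 points in 13.7% of combinations and is exactly 0 in only 0.6%.
- The worst case can be checked by hand. Start on a Sunday with phases of 20, 9, 12 and 9 days; these hold 5, 4, 2 and 4 weekend days. Then B − A = (4/9 + 4/9)/2 − (5/20 + 2/12)/2 = 0.444 − 0.208 = 0.236.

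**3. Effect on one patient's contrast.** The shift is g × (difference in share). For a 1-point weekend effect on SCS it is about 0.07 (SD) and 0.24 at worst. With independent days the sampling variance of the contrast is 2 × ¼ × Σ(1/phase length), which gives a standard error of about 0.43 on average. The target is 2.

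**4. Per-patient power.** I simulated the randomization test with all 2300 schedules as the reference set, 21,000 runs per setting (Monte Carlo error about 0.2-0.3 points). Entries are power in %, phase-mean test / same test after subtracting the patient's day-type means. A Unity effect of 1.41 daily SD corresponds to the plan's 2 points.

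| Unity effect (daily SD), rho | g = 0 | g = 0.7 SD | g = 1 SD | g = 2 SD |
|---|---|---|---|---|
| 1, 0 | 67.7 / 67.1 | 65.5 / 67.1 | 63.1 / 67.1 | 53.1 / 67.1 |
| 1, 0.3 | 53.8 / 53.2 | 51.9 / 53.2 | 50.5 / 53.2 | 43.9 / 53.2 |
| 1.41, 0 | 89.4 / 89.0 | 87.8 / 89.0 | 86.0 / 89.0 | 76.6 / 89.0 |
| 1.41, 0.3 | 79.5 / 79.0 | 77.7 / 79.0 | 76.2 / 79.0 | 67.7 / 79.0 |

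The loss is 1.2-1.6 points at 0.7 SD, 2.7-4.0 at 1 SD and 9.3-14.0 at 2 SD. With no weekend effect the adjustment costs 0.4-0.6 points. With no Unity effect, rejection is 4.8-5.1% in every setting, adjusted or not.

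**5. Group level.** The plan's 16.35 subjects reproduces with a noncentral t at variance 5.3 + 2×2/2 = 7.3. Weekend imbalance adds 0.0674² × g² = 0.0045 g². At g = 2 points this is 0.018, and power with 20 patients goes from 88.1% to 88.0%.

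**The case against.** The strongest reply is that the article states nothing false. It promises a weekend in each period, which holds, and never claims equal shares. A day-type covariate could also sit in a fuller protocol or analysis plan not shown here. Both points stand and keep this minor. Against them, the article does fix the test statistic, and its Discussion relies on publication to hold the methods unchanged, so the adjustment is best stated in advance.

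Three stronger readings are tempting, and the documents support none of them.

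- **False positives.** A reader might infer that a weekend effect will be mistaken for a Unity effect. Among the roughly 14% of schedules with more than 10 points of imbalance, null rejection is indeed about 7-13% for weekend effects of 1 to 2 daily SD. That rate is conditional on an uneven schedule and is offset elsewhere. Calendar effects are the same under every possible assignment, so the randomization test keeps its overall 5% level.
- **Group bias.** If every patient started on the same weekday, the mean difference in share would be at most 3.4 points (+3.4 for Monday, −3.4 for Friday). Nothing in the article says they do; recruitment is non-concurrent in four centres. Even then, a 1-point weekend effect would move the SCS contrast by 0.034 against a target of 2.
- **A material threat to the primary outcome.** The plan names activity level, not comfort, as what varies. A weekend effect of 1 daily SD on SCS would be about 1.4 points and one of 2 SD about 2.8 points, which is more than the Unity effect sought. Such effects are more plausible for steps and wearing time.

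**Conclusion.** The point holds as a minor issue of per-patient precision. The 7-day minimum does not balance weekend days, and the stated test leaves the imbalance in nearly every patient's contrast. The size depends on a weekend effect that the article does not give: about 0-2 power points lost for effects up to 0.7 daily SD (about 1 SCS point), 2-4 at 1 SD and 9-14 at 2 SD. These figures assume a two-sided test and autocorrelation of 0 or 0.3. The point is worth acting on mainly for steps per day and wearing time. It is minor for SCS and negligible for the aggregated estimate. The validity of the test is not in question. The change is optional but cheap.

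**What to change.** In the per-patient analysis section, add for the daily outcomes: subtract from each daily value the patient's own mean for that day type (weekday or weekend), then compute phase means and re-randomise over the same 2300 schedules. The adjustment uses only the calendar and not the assignment, so the test stays exact.

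Take the reported effect size from a model with a weekend indicator rather than from the adjusted values, which shrink it slightly (by about 0.5% on average and 6% at most over the enumerated schedules). A weekend term in the hierarchical model is optional.

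The cost is a sentence or two and a few lines of code, with no new data, visits or patients, and under about 1 power point if no weekend effect exists. Whole-week phases would be a worse remedy: over 49 days they leave C(6,3) = 20 schedules and a smallest p of 1/20 = 0.05.
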